## Abstract

**Background:**

Falls are common among community-dwelling elderly people and can have a considerable impact on quality of life and healthcare costs. People who have sustained a fall are at greater risk of falling again.

We replicated a British randomised controlled trial which demonstrated the effectiveness of a multidisciplinary intervention programme to prevent falls.

The objective is to describe the design of a replication study evaluating a multidisciplinary intervention programme on recurrent falls and functional decline among elderly persons at risk. The study consists of an effect evaluation, an economic evaluation and a process evaluation.

**Methods/design:**

The programme is aimed at community-dwelling elderly people aged 65 years or over who have visited an accident and emergency department (A&E department) or a general practitioners' cooperative (GP cooperative) because of a fall.

The design involves a two-group randomised controlled trial. Participants are followed for twelve months after baseline. The intervention programme consists of a detailed medical and occupational therapy assessment with referral to relevant services if indicated. People in the control group receive usual care.

The main outcome measures of the effect evaluation are number of falls and daily functioning. The economic evaluation will be performed from a societal perspective. A process evaluation will be carried out to evaluate the feasibility of the intervention programme.

## Background

### Publishing the design of a study

This article describes the design of a replication of a randomised controlled trial (RCT) evaluating the effectiveness and cost-effectiveness of a multidisciplinary intervention programme to prevent further falls among elderly people at risk.

Publishing the design and protocol of a study before results are available is important for several reasons. A published protocol allows easier comparison between what was originally intended and hypothesised and what was actually done [1], and it gives readers greater insight into the methodological quality of a study. Furthermore, it has often been recognised that negative or adverse outcomes are less likely to be published [1-3]. Publishing the design of a study before its start announces that a study will be undertaken, which encourages publication of the results and in any case informs researchers where they can find the data for inclusion in systematic reviews [1,2]. Thus, publishing a design article can prevent publication bias.

### Prevention of falls

About one-third of people over the age of 65 fall at least once a year [4]. People who have fallen show an increase in morbidity, mortality and healthcare utilisation [5], which implies increased healthcare costs. In addition, people who have sustained a fall are at greater risk of falling again [5].

Since preventing falls has been a matter of interest for years, many programmes aimed at preventing falls have been developed and evaluated. Unfortunately, many of these have turned out to be ineffective [4]. However, there is now considerable evidence of the effectiveness of multifaceted interventions. Programmes likely to be effective in preventing falls among elderly people are multidisciplinary, multifactorial programmes screening for health and environmental risk factors and offering interventions, both for the general population of community-dwelling elderly people and for elderly people with a history of falling selected because of known risk factors [4]. An example of such an intervention programme is the successful programme developed by Close et al. [5]. This programme is aimed at people aged 65 years or older who live in the community and have visited an accident and emergency department because of a fall. The intervention programme consists of a detailed medical and occupational therapy assessment with referral to relevant services if indicated. The intervention has been evaluated in a randomised controlled trial, which demonstrated that this multidisciplinary intervention implemented among people at risk was highly effective in reducing the number of recurrent falls and associated injuries in London (United Kingdom) [5].

Because details of the status of the participants, the context of the intervention and the content and presentation appear to be critical, it has been recommended to re-evaluate effective intervention programmes in different healthcare systems [4]. We therefore decided to evaluate the effectiveness of the intervention developed by Close [5] in Dutch healthcare, by replicating this study in the Netherlands.

### Objective and research questions

The main objective of our current study is to evaluate the effects of a multidisciplinary intervention programme on recurrent falls and functional decline among elderly persons who have visit a general practitioners' cooperative (GP cooperative) and/or an accident and emergency department (A&E department) because of a fall. This objective has resulted in the following research questions.

• Is a multidisciplinary intervention programme more effective than usual care in preventing new falls and functional decline among community-dwelling elderly people who visit a GP cooperative and/or A&E department at a hospital because of a fall?

• Is the multidisciplinary intervention programme cost-effective compared to usual care when assessed from a societal perspective?

Besides the effect evaluation and economic evaluation, a process evaluation is being carried out to assess the feasibility and applicability of the intervention programme for those receiving and implementing the intervention.

## Design and methods

### Design

Figure 1 shows the design of the study presented, which is a two-group randomised controlled trial. At this stage, the randomisation process has already been completed. Randomisation was achieved by means of computerised alternative allocation and performed by an external agency. Randomisation took place after completion of a self-administered baseline questionnaire. People allocated to the control group received usual healthcare, while people in the intervention group underwent a medical and occupational therapy assessment. The intervention period is scheduled to last for a maximum of 3.5 months after the baseline measurement. After baseline measurement, all subjects are followed for a twelve-month period. During this follow-up period, falls and healthcare utilisation are measured continuously. Subjects are contacted monthly by telephone for an interview about their falls and healthcare utilisation. In addition, self-administered questionnaires are sent to the subjects after four and twelve months.

**Figure 1 F1:**
[figure not shown]
Study Design

We have taken various measures to ensure blinding in the data collection process. Questionnaires are collected anonymously and sorted by number. Follow-up measurements by phone are contracted out to an independent call centre, whose operators are unaware whether the subjects have been allocated to the intervention or the control group.

The study design and protocols were approved by the Medical Ethics Committee of the University Hospital and University of Maastricht.

### Target population

Various studies have been conducted to assess the effectiveness of programmes to prevent falls. Although most studies were aimed at the general population of elderly people, details of the status of the participants appear to be critical [4,6]. Several authors have suggested that interventions are likely to have greater effect when targeting people at risk [7,8]. People who attend an A&E department with an injurious fall form a high-risk group, and are expected to be more receptive to an intervention programme aimed at reducing falls than the general population of community-dwelling elderly people. In a study by Close et al., about half of the patients who attended an A&E department with a fall had experienced an earlier fall in the previous year, compared to about one third of the elderly people in the general population [5]. Like Close et al. [5], we chose community-dwelling elderly people aged 65 years or over who had sustained an injurious fall as the target population of our intervention programme. The following definition of a fall was used: 'A fall is an event which results in a person coming to rest inadvertently on the ground or other lower level'. This definition is derived from that used by the Kellogg International Work Group [9].

### Recruitment of the study population

Recruitment of subjects took place at the local GP cooperative and the A&E department of the University Hospital in Maastricht. The Maastricht GP cooperative is a group of GPs from practices in the town of Maastricht and the surrounding area who have founded a non-profit organisation to provide care for their own patients after hours [10]. The Maastricht GP cooperative has been set up at the hospital's A&E department and covers the out-of-hours service for all local GPs [11].

The following inclusion criteria were used: age 65 years or older, community-dwelling, having visited the A&E department or GP cooperative at the University Hospital Maastricht for the consequences of a fall, and living in Maastricht or its surrounding area. People were only allowed to enter the programme after completing and returning an informed consent form. Exclusion criteria were: not able to speak or understand Dutch, not able to complete questionnaires or interviews by telephone, cognitive impairment (a score of less than 4 on the Abbreviated Mental Test 4 (AMT 4) [12,13], long-term admission to a hospital or other institution (more than four weeks from the date of inclusion), permanently bedridden, or fully dependent on a wheelchair.

### Sample size calculation

Sample size calculations were based on the expected effects of the intervention on the main outcome measure, the percentage of people sustaining a fall during one year of follow-up. The study by Close et al. [5] found that the percentage of persons who sustained a recurrent fall was 52% in the usual care group and 32% in the intervention group. If we want to detect the same reduction in the percentage of persons sustaining a recurrent fall in our study, with a power (1-beta) of 90% and alpha of 0.05, we need 123 patients in each group (a total of 246). Based on the experiences of Close et al. and our own experiences in trials among elderly people in the Netherlands [14], we expect a dropout rate of about 25% during the one-year follow-up period. This means that about 164 persons per group (a total of 328) have to be included in the study. The inclusion period was 14 months.

### Intervention programme

To adapt the programme developed by Close et al. [5] to the Dutch situation, and to make improvements based on recent insights, we performed a review of the literature, convened a consensus meeting and tested the adapted version in a pilot study (n = 36). Based on this process, we made some improvements to Close et al.'s programme.

The final programme includes a medical and occupational therapy assessment resulting in recommendations. The medical assessment consists of an examination performed by a geriatrician, a geriatric nurse and a rehabilitation physician to identify and address risk factors for falling. The examination includes a comprehensive general examination, but in addition focussed on a more detailed assessment of visual acuity, stereoscopic vision, mobility, balance, cognition, affect, use of medication and examination of feet and footwear. Recommendations or indications for referral resulting from this examination are sent to the patient's GP. After the medical assessments, an occupational therapist visits the patients to identify possible risk factors for falling in the home environment. The therapist makes recommendations regarding adaptations to the home environment, assistive devices, home care and behavioural change. Recommendations by the occupational therapist are sent directly to the subjects themselves and to their GPs. As stated before, the intervention period is scheduled to last for a maximum of 3.5 months after the baseline measurement.

An important addition to Close et al.'s protocol [5] is the collaboration with a rehabilitation physician (physiatrist) in the medical part of the intervention. In addition to the screening by a geriatrician, our programme also involves screening by a rehabilitation physician who examines the subjects' feet and the shoes which the subjects wore at the time of the fall. Details of the process of adaptation and the contents of the intervention programme will be published elsewhere.

### Usual care in the Netherlands

People in the control group receive usual care. At present, no guidelines exist for the systematic assessment of the underlying causes of an injurious fall presented at an A&E department or GP cooperative in the Netherlands. In usual care, medical risks and other risk factors such as environmental hazards in the home and patients' risk behaviour are not systematically registered and addressed by hospital physicians, specialists or general practitioners. Moreover, no systematic attention is currently being paid to the specific consequences of an injurious fall for the daily functioning of individual patients in their unique situation. We placed no restrictions on co-interventions.

### Effect evaluation

The primary outcome measures of the effect evaluation are number of falls and daily functioning. Number of falls is subdivided into three separate measures: the percentage of elderly people sustaining a fall during the one-year follow-up period, recurrent falls during follow-up (i.e., the percentage of elderly people sustaining two or more falls), and injurious falls during follow-up (the percentage of elderly people receiving medical care after a fall). Falls are recorded continuously by means of a fall calendar during the twelve-month follow-up period. Subjects are called monthly to report their falls as recorded on the fall calendar relating to the previous month.

We decided to measure daily functioning by means of the Frenchai Activity Index (FAI) [15], in contrast to Close et al. [5], who used the Barthel Index. Our reason for choosing this instrument was that the FAI has proved to be suitable for the general population of elderly people [14] and has at least two advantages over the Barthel Index. One is that the Barthel Index shows a ceiling effect when applied to elderly people who have sustained a fall [5]. The other is that most activities of daily living (ADL) scales, like the Barthel Index, do not refer to complex activities like housekeeping, recreation, hobbies and social interaction. These so-called instrumental abilities (IADL) may affect the quality of life considerably, and the FAI focuses primarily on these IADL abilities [15]. The FAI is measured by means of self-administered questionnaires at baseline and after four and twelve months.

Our secondary outcome measures are: recuperation from the fall, health complaints, perceived health measured by means of the first two items of the RAND-36 [16], ADL and IADL disability measured by means of the GARS (Groningen Activity Restriction Scale) [17], mental health measured by means of the HADS (Hospital Anxiety and Depression Scale) [18,19] and quality of life measured by means of the European Quality of Life instrument (EuroQol) [20]. The secondary outcome measures are assessed by means of self-administered questionnaires at four and twelve months.

Besides the primary and secondary outcome measures, we assess some background variables which are considered to be predictors, confounders or effect modifiers. The following personal characteristics are assessed: age, sex, marital status, living alone and socio-economic status. In addition, we assess the circumstances and causes of the falls reported at the GP cooperative and/or A&E department, the consequences of the falls (using the Falls Handicap Inventory [21]), the type of injury, falls in the previous year (retrospective), the patient's height, weight, use of medication and social contacts (using an adjusted version of items 4 and 5 of the Rand Social Health Battery)[22,23], and the occurrence of life events. All background variables are measured at baseline.

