### Analysis

Data will be primarily analysed according to the intention-to-treat principle, i.e., including all participants with valid data, regardless of whether they received or did not receive the intervention. Subsequently, the results of the intention-to-treat analysis will be compared with the results of an on-treatment analysis, to assess whether protocol deviations have caused bias. Participants with documented deviations from the study protocol (i.e., participants in the intervention group who did not receive the entire intervention or participants in either the intervention or the control group with incomplete follow-up data) will be excluded from this on-treatment analysis.

Comparability between the intervention and control groups will be assessed at baseline to check for differences between the two groups. Outcome at four and twelve months will be compared between the intervention and control groups by both univariate and multivariate techniques. We will use multivariate analysis to adjust for possible differences in baseline scores and background variables between the intervention and control groups. Dropouts and losses-to-follow up will be described.

The economic evaluation will involve calculating cost-effectiveness and cost-utility ratios. The additional costs and additional benefits of the intervention programme compared with usual care will be examined by calculating incremental cost-effectiveness and cost-utility ratios. These incremental ratios represent the difference in mean costs between the intervention and usual care groups in the numerator and the difference in mean effects in the denominator[27].

Since the recruitment period is only 14 months, and the follow-up period is also relatively short (12 months), it is unlikely that there will be substantial differences between costs made by and for patients who started in the first part of the recruitment period and those who started in the last part. Therefore, discounting of costs is not required. Finally, a sensitivity analysis will be done to assess the generalisability of the assumptions made in the costing process. This sensitivity analysis, which involves calculating the upper and lower limits of the confidence interval of cost and effect variables, will allow us to explore and quantify the uncertainty not related to sampling variations.

The process evaluation will mainly be analysed by means of descriptive techniques.

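### Four outcomes are declared primary but the trial is sized on one, with no rule for which decides effectiveness and with *recurrent fall* used in two senses

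*Protocol article*

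**What the plan says.** The Effect evaluation section of the protocol article opens: "The primary outcome measures of the effect evaluation are number of falls and daily functioning. Number of falls is subdivided into three separate measures". The three falls measures are the percentages of participants with any fall, with two or more falls, and with a fall that led to medical care, all over one year. Daily functioning is the fourth primary outcome: "The FAI is measured by means of self-administered questionnaires at baseline and after four and twelve months". The Analysis section adds: "Outcome at four and twelve months will be compared between the intervention and control groups by both univariate and multivariate techniques". Neither visit is named as the deciding one. The Methods part of the abstract also speaks of main outcome measures in the plural.

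The Sample size calculation section uses the singular. It is built on "the main outcome measure, the percentage of people sustaining a fall during one year of follow-up", with alpha 0.05 and 90% power, and arrives at 123 per group, or 164 after 25% dropout. Its rates come from the earlier British trial, where "the percentage of persons who sustained a recurrent fall was 52% in the usual care group and 32% in the intervention group". The Effect evaluation section gives that term another meaning: "recurrent falls during follow-up (i.e., the percentage of elderly people sustaining two or more falls".

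**The concern.** Two sections of the same document fix the primary outcome in incompatible ways. One names a single main outcome and gives it a power statement. The other gives equal standing to four, one of them with two post-baseline visits.

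The research question in the Objective section joins new falls and functional decline but does not say whether success on either is enough or both are needed. Each reading has a cost. If any one outcome suffices, 0.05 is not the error rate of the trial's conclusion. If both are needed, the stated 90% for any fall is not the power of the trial. The Discussion ties implementation in usual care to shown effectiveness and cost-effectiveness, so the decision rule has practical weight.

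The label matters separately. Read with the protocol's own definition, the power is stated for any fall using rates for two or more falls.

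**Working it through.** **Inputs from the document.** Rates 52% and 32%, alpha 0.05, power 90%, dropout 25% (Sample size calculation); three falls measures plus the FAI as primary, FAI at 4 and 12 months (Effect evaluation, Analysis); 166 and 167 participants allocated (Progress of the study). Sidedness is not stated.

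**Step 1: reproduce the plan's figure.** Two-sided formula with unpooled variance:

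n = (1.96 + 1.2816)² × (0.52×0.48 + 0.32×0.68) / 0.20² = 10.508 × (0.2496 + 0.2176) / 0.04 = 122.7, so 123 per group.

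Dropout: 123 / 0.75 = 164. Both figures match. The pooled-variance version gives 126. One-sided versions give 103 (113 with continuity correction) and do not match, so the plan's 0.05 is two-sided, with 2.5% in the favourable direction.

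**Step 2: count the comparisons.** Three falls measures and the FAI once make four. Counting the FAI at both visits makes five.

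**Step 3: error if each were tested at two-sided 0.05 and all were independent.**

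- At least one significant result in either direction: 1 − 0.95⁴ = 18.5% for four; 1 − 0.95⁵ = 22.6% for five.
- At least one significant result favouring the intervention: 1 − 0.975⁴ = 9.6% for four; 1 − 0.975⁵ = 11.9% for five.

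**Step 4: allow for correlation.** The outcomes are not independent, because everyone with two or more falls, or with a medically treated fall, also counts under any fall. The document gives no correlations, so these were assumed and varied. The null was simulated with 125 per group in six scenarios of 20,000 trials each. Any-fall rate was 52% (42% in one scenario). The share of fallers with two or more falls was 35–60%, and the chance of medical care for a single fall 15–60%. Correlation between FAI visits was 0.5–0.8, and between fall tendency and FAI 0–0.3 in size. The falls test statistics then correlated at 0.37–0.79.

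| | Four comparisons | Five comparisons |
|---|---|---|
| Any significant result, either direction | 15.3–17.2% | 17.7–20.7% |
| At least one favouring the intervention | 7.6–8.7% | 8.7–10.6% |

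Rounded over both counts, this is about 15–21% in either direction and about 8–11% in favour. A single test has 5% and 2.5%.

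**Step 5: what an equal split would cost.** At 0.05/4 = 0.0125, power for any fall at 123 per group falls to about 76–77%, depending on the variance formula. Keeping 90% would need 172 per group by the pooled formula, or 172 / 0.75 = 229.3, so 230 with dropout. With 333 participants already allocated, that is out of reach. A single primary outcome keeps 123 and 164.

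**Step 6: the label.** The sizing section names any fall as its outcome, then quotes rates for a recurrent fall and aims to detect the same reduction in that. Under the Effect evaluation definition this would be two or more falls. If so, the control rate for any fall could not be below 52%, but neither its value nor the difference between groups is given, and the power for any fall could not be recovered from the document.

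**The case against.** The strongest reply is that this is a condensed article and its analysis plan is not shown, so a hierarchy or a split of alpha may exist elsewhere. That stands as far as it goes: the absence of an adjustment method is not in itself a finding. The document does not say that each primary outcome is tested at 0.05, and the figures above are conditional on that. What remains is that two sections of this document disagree about which outcome is primary, and an adjustment in another document would not reconcile them.

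Three stronger readings are tempting and are not supported.

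- A reader might take 15–21% as the chance of a false claim that the programme works. That figure includes apparent harm. The favourable part is about 8–11%, at most 11.9% for five independent comparisons.
- A reader might count the univariate and multivariate analyses as two chances of success. The Analysis section describes the second as adjustment for baseline differences, so it is not counted here. Nor does the text say that the FAI at either visit alone would establish success, which is why four and five comparisons are both shown.
- A reader might conclude that the trial was sized on the wrong rates. Everyone had fallen at entry, so a recurrent fall in the sizing section may simply mean a new fall after the index fall, and the Objective section speaks of new falls. What the earlier trial measured cannot be settled from this document.

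It also counts for the plan that the Economic evaluation section makes the percentage with a fall in one year the primary outcome for cost-effectiveness, the same measure that the sizing singles out. That section does not govern the effect evaluation, but it shows which choice fits best.

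**Conclusion.** The point holds as a contradiction within the protocol that should be fixed. Four outcomes are declared primary, one of them compared at two visits; one is sized; no rule says which decides effectiveness. On the condition that each is tested at two-sided 0.05, the chance of a nominally significant result favouring an ineffective programme is roughly three to four times that of a single test (8/2.5 = 3.2; 11/2.5 = 4.4 at the top of the range). That multiple rests on assumed correlations. The contradiction itself rests on the text alone. The sample size arithmetic is correct. The conflict over *recurrent fall* is certain as a matter of wording; whether it affects the power is unknown.

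**What to change.** In the Effect evaluation section, name at least one fall during 12 months as the single primary outcome of the effect evaluation, tested at two-sided 0.05. This agrees with the Sample size calculation and Economic evaluation sections and leaves 123 per group (164 with dropout) unchanged. Make two or more falls, medically treated falls and the FAI secondary, or test them in a prespecified order, with the FAI visit stated. The documents give no basis for one order over another, so that choice belongs to the investigators. Align the abstract.

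In the Sample size calculation section, replace *recurrent fall* with *at least one new fall* if that is what the 52% and 32% measured. Otherwise restate the power for any fall.

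Both are wording changes and must be settled before outcomes are analysed; the article states that follow-up was to end in May 2005. The price is that effectiveness can no longer be claimed on daily functioning or another falls measure alone.
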